#### Secondary objectives

We will analyze whether there is a statistically significant clinical improvement in the intervention group in comparison to the control group in terms of:

1. Negativization of the D-H test at a week, a month and a year follow-up.

2. Answer to the dichotomous (yes/no) question regarding presence of vertigo in the previous week.

3. Number of new episodes of vertigo between medical visits.

4. Time from the baseline visit to the first new episode.

5. Rate of vertigo severity on a 10 point-Likert scale: 0 = no symptoms of vertigo; 10 = most severe and unbearable.

6. Quality of life measured with the specific questionnaire Dizziness Handicap Inventory- Short form (DHI-S).

7. Amount of betahistine tablets taken, according to the patients’ self-registers.

8. Days of temporary disability due to vertigo or other causes, recorded on the electronic medical record.

### Design

This is a controlled randomized clinical trial, which will be conducted by GPs who will have previously received a two-hour training to perform the repositioning maneuvers under the supervision of an ENT specialist. Patients will be reassessed one week, one month, and one year after the first visit by a different GP from the one who performed the first visit, in order to accomplish blinding of both study participants and personnel.

### Study’s scope

Two urban primary care centers which provide care for a population of approximately 49,400 people.

### Study sample

All patients with newly diagnosed BPPV, who attend our two primary care centers, will be potential participants in our clinical trial. Patients will be systematically recruited with the collaboration of the 26 GPs who work at the two participant primary care centers. Regardless the initial cause for the visit, if a GP suspects BPPV, he/she will check whether the patient meets the inclusion criteria and presents no exclusion criteria. Eligible participants will be informed of the possibility to take part in the trial and will be supplied with written information about the study. Those who accept to participate in the study will be given an appointment for the baseline visit, preferably within a week and no longer than ten days after. The recruitment period is expected to last two years (Figure 1).

**Figure 1 F1:**
[figure not shown]
Flow diagram of the study.

### Inclusion criteria

Patients aged 18 years and older who attend our primary care centers, with suspected diagnosis of BPPV, and present vertigo or nystagmus following the D-H maneuver. All other causes of vertigo should be ruled out through clinical history assessment and review of the electronic medical record. Written informed consent will be obtained from all subjects, of both the intervention group and the control group, prior to their inclusion in the study.

### Exclusion criteria

The exclusion criteria, which will be detected through the clinical history, physical examination and review of the electronic medical record, are:

1. Previous or current diagnoses of labyrinthine diseases such as Ménière’s disease, labyrinthitis or vestibular neuronitis.

2. Contraindications to canalith repositioning procedures: cervical spinal stenosis, severe kyphoscoliosis, limited cervical mobility, Down syndrome, advanced rheumatoid arthritis, cervical radiculopathies, Paget’s disease, morbid obesity, ankylosing spondylitis, severe lumbar dysfunction and spinal cord injuries.

3. Pregnancy or breastfeeding.

4. Contraindications to betahistine administration.

5. Patient refusal to participate in the study.

6. Non-residence in the study area.

7. Other causes which may hinder the understanding of the objectives and methodology of the trial (language, low educational level, and so on).

### Sample size

Accepting an alpha risk of 0.05 and a beta risk of 0.2 in a bilateral contrast, sample size calculations determined a need for approximately 75 subjects in each group (the intervention group and the control group), in order to detect a statistically significant difference in the improvement rate between the two groups (30% for the control group and 55% for the intervention group) at follow-up. We estimated a 20% rate of loss in participants (objectives 1 and 2). This sample size also enables us to evaluate 1-point clinical improvement in the intervention group compared to the control group, assuming a standard deviation of 1.9 (objectives 3,5,6,7 and 8). We estimated a recurrence hazard ratio of 0.5 in the intervention group, assuming that 30% of patients in the control group will have relapsed after one year. The software used for the calculation was GRANMO version 7.12. The software used for the calculation was GRANMO version 7.12 (Program of Research in Inflammatory and Cardiovascular Disorders. Institut Municipal d’Investigació Mèdica, Barcelona, Spain).

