### Follow-up visits 2, 3 and 4 to all patients

The second visit will take place 1 week after visit 1. Visits 3 and 4 will be performed 1 month, and 1 year after visit 1, respectively. Telephone reminders will be used to reduce patients’ loss during follow-up.

Follow-up visits will include:

•Bilateral D-H maneuver. Outcome measures will be: nystagmus (yes/no) and vertigo (yes/no).

•Assessment and record of number of new episodes of vertigo, and time (in days) from the baseline visit to the first new episode. This information will be obtained through an accurate medical history, and review of the patient’s electronic medical record, including visits to the emergency department, in our medical centers as well as in other emergency centers. Outcome measures will be: vertigo (yes/no), number of episodes, and intensity of symptoms on a 0 to 10-point Likert scale.

•Registration of the total score on the Dizziness Handicap Inventory-Short form (DHI-S)

•Count of tablets of betahistine taken

•Record of new medication taken, for any cause, from visit 1

•Registration of days of temporary disability during the previous year caused by vertigo or any other cause, in employed participants

•Record of medical consultations due to dizziness.

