### Statistical analysis

Data will be analyzed in accordance with the CONSORT guide for cluster randomized trials, and all analyses will be performed on an intent-to-treat basis [28].

Firstly, the intervention group and control group will be analyzed for baseline comparability according to the baseline variables. Descriptive statistics of all studied variables will be presented in contingency tables. Pearson’s Chi-square test or Fisher’s exact test will be applied to assess categorical variables. Student’s *t-*test or ANOVA will be used if the variables follow a normal distribution and Mann–Whitney *U*-test if they do not (objectives 1 and 2).

A multilevel logistic regression analysis will be performed to evaluate the association between the dependent variable (cured/not cured) and the independent variable (group assigned), adjusting potential confounders.

A multivariate linear regression model will be conducted to evaluate change in the Likert scale and quality of life inventory (DHI-S), (objectives 5 and 6); and a Poisson or Binomial negative distribution (for of outcome variables in case of over-dispersion) will be used to compare number of vertigo episodes, number of tablets consumed, days of temporary disability and days with symptoms (objectives 3, 7 and 8).

In order to evaluate D-H test’s intra- and inter-observer variations, corresponding Kappa ponderate indexes (Kp) and intra-class correlation coefficients (ICC) will be calculated. Intra-observer variations will be determined through comparison of the D-H test’s results, performed twice on each patient, after a five-minute interval, for a total number of ten patients per observer, in any visit. Inter-observer variations will be determined through comparison of the D-H test’s results on each patient, conducted by pairs of observers, after a five-minute interval, for a total number of ten patients per pair of observers, in any visit. The estimated number of observers will be 10 to 12. Homogeneity and concordance in the Epley’s maneuver performance will be evaluated by an expert external auditor, who will assess between two and three video-registered maneuvers carried out by each observer.

We will apply the Cox regression model to explore the effect of the intervention (Epley’s maneuver) on the survival (that is interval between two vertigo episodes) (objective 4).

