### Study limitations

Frentzel glasses (a diagnostic tool to evaluate nystagmus) were not used in the study in order to achieve a more realistic approach in the diagnosis of BPPV in primary care. GPs’ lack of experience in ENT skills may reduce reliability of the maneuvers but it resembles usual practice in primary care settings. Therefore, study patients who only experience vertigo and do not present nystagmus during the D-H test will not be excluded from inclusion (as performed in other studies) [29]. As we mentioned on the D-H test results section, we will consider both vertigo with nystagmus and vertigo without nystagmus as positive D-H results; the reason being that GPs’ lack of experience in ENT skills, and not using the Frentzel glasses may diminish the D-H test sensitivity by missing less clear cases of nystagmus. This factor, however, will be accounted for by evaluating these patients separately.

Betahistine administration during the course of treatment can speed up the recovery of these patients [25,26] and may also be useful to evaluate the results of the study. To avoid bias in our trial, all patients from both groups (intervention and control), will be prescribed betahistine 8 mg on a *pro re nata* (PRN) basis, up to three times a day until improvement of symptoms. Each participant will be given a notebook in order to record the number of tablets taken between visits. From an ethical point of view, we believe that leaving patients untreated, apart from the sham maneuver is an arguable point.

The incidence of BPPV may hinder securing an adequate sample size. However, internal data from computerized clinical records indicates that this disorder is much more frequent than previously reported in the literature. Moreover, BPPV prevalence increases with age, reaching 10% in individuals over 80 years old [4].

As this trial evaluates a therapeutic maneuver, the blinding achieved in this study may not be comparable to that of a double-blind pharmacological trial. On the other hand, GPs may present lower skills than experienced ENT specialists, in assessing nystagmus, performing the D-H test and the Epley’s repositioning maneuver. Even though some authors support that GPs are qualified to perform these skills [29], this factor will be controlled measuring the inter-observer and intra-observer variability for each maneuver and evaluation, and including ‘observer’ as a potential confounder in a multilevel logistic regression.

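### One sample-size calculation (1 point, SD 1.9) is claimed for five outcomes in different units; it can match at most a point-scored outcome, and the power claim is unsupported for the others

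*Protocol article*

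**What the plan says.** The Sample size section sets the error rates: "Accepting an alpha risk of 0.05 and a beta risk of 0.2 in a bilateral contrast". It arrives at "approximately 75 subjects in each group (the intervention group and the control group"), from improvement rates of "30% for the control group and 55% for the intervention group) at follow-up". It then allows for attrition: "We estimated a 20% rate of loss in participants (objectives 1 and 2"). The next sentence says that this number also allows a 1-point clinical improvement to be evaluated, "assuming a standard deviation of 1.9 (objectives 3,5,6,7 and 8"). No other effect size or standard deviation is given for those five objectives.

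The list of secondary objectives shows what they are:

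- objective 3: number of new vertigo episodes between visits
- objective 5: severity on a 0-10 scale
- objective 6: DHI-S score
- objective 7: betahistine tablets taken
- objective 8: days of temporary disability

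The Statistical analysis section plans linear regression for objectives 5 and 6. For the rest, a Poisson or negative binomial model "will be used to compare number of vertigo episodes, number of tablets consumed, days of temporary disability and days with symptoms (objectives 3, 7 and"; the list closes with objective 8. The follow-up visit list restricts the disability record to days "caused by vertigo or any other cause, in employed participants". Study limitations states that betahistine is taken as needed, "up to three times a day until improvement of symptoms".

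**The concern.** A difference of one point with a given SD has meaning only on the scale that the SD came from. Episodes, tablets and days are not points, and nothing in the protocol suggests that they share an SD with a 0-10 rating. Three of the five outcomes are also to be tested as rate ratios, which a mean-difference calculation with a common SD does not size. One is observed in only part of the sample.

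At stake is how null results will be read. The sentence follows directly on a calculation at 80% power, so it reads as a claim of about that power for all five outcomes. A null finding on tablets, episodes or disability days could then be taken as an adequately powered negative. These outcomes are not marginal: the primary objective counts subjective vertigo, quality of life and tablet use as parts of clinical improvement, and the Background names temporary disability and medication among the expected gains.

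**Working it through.** **Inputs from the protocol.** Two-sided alpha 0.05; power 0.80; 75 per group; 20% loss, so 75 × 0.8 = 60 evaluable; difference 1; SD 1.9; control relapse 30% at one year; recurrence hazard ratio 0.5. **Assumed, because not given:** employed share, SD of tablets, episodes per relapser.

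**Reproducing the main figure.** For 30% versus 55%, the arcsine formula gives 60 per group, and 60 / 0.8 = 75. The pooled normal formula gives 61, or 77 after loss. The stated number reproduces.

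**Reproducing the 1-point claim.** n = 2 × (1.960 + 0.842)² × 1.9² / 1² = 56.7, so 57 per group; 56.7 / 0.8 = 70.8, which fits within 75. Noncentral-t power for 1 point at SD 1.9 is 82% with 60 per group and 89% with 75.

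**Slack.** The detectable difference at 60 per group is 2.802 × SD × √(2/60) = 0.51 × SD. For this to be 1 unit or less, SD must be about 1.95 or less. With all 75 per group the limit is about 2.19. The claim therefore holds only for outcomes whose SD is close to 1.9 or smaller.

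**Objective 8 (days, employed only).** Keeping SD 1.9 and a 1-day difference:

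| Employed share (assumed) | n from 60 | Power | n from 75 | Power |
|---|---|---|---|---|
| 70% | 42 | 66% | 52.5 | 76% |
| 50% | 30 | 52% | 37.5 | 61% |
| 40% | 24 | 43% | 30 | 52% |

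By the formula above, 80% power needs 56.7 employed per group: 56.7 / 60 = 94% of evaluable patients, or 56.7 / 75 = 76% of all randomised.

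**Objective 7 (tablets).** At one tablet per intake (assumed), three intakes a day give a range of 0 to 21 in week 1. If use were spread evenly over that range (assumed), SD = 21 / √12 ≈ 6. Power for a 1-tablet difference at 60 per group is then about 15%, and 80% power would need 2 × 2.802² × 6² ≈ 565 per group.

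**Objective 3 (episodes).** The same paragraph assumes 30% relapse in controls and a hazard ratio of 0.5. That implies 1 − 0.70^0.5 = 16.3% relapse in the intervention group, a difference of 13.7 percentage points. Suppose that relapse means at least one new episode, and that every relapser in either group has k episodes (both assumed).

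- Mean difference = 0.137k, so a 1-episode difference needs k = 1 / 0.137 ≈ 7.3.
- Control SD = 7.3 × √(0.30 × 0.70) = 3.35; intervention SD = 7.3 × √(0.163 × 0.837) = 2.71; pooled SD ≈ 3.05.
- Power at 60 per group ≈ 43%.

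Both difference and SD scale with k, so this 43% does not depend on k. Even if the intervention abolished every episode, a 1-episode difference would need 1 / 0.30 = 3.3 episodes per relapsing control.

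**Objective 6 (DHI-S).** No SD or score range is given, so power for 1 point cannot be computed.

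**Objective 5 (0-10 severity).** The calculation fits if the SD is 1.9.

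**The case against.** The strongest reply is that there is no arithmetic error. The 57 per group is correct, the sample size comes from objectives 1 and 2, and the five outcomes are listed as secondary. All of that stands.

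It can also be said that outcome-specific inputs may sit in the full protocol that this article condenses. That is possible, but the point is not that inputs are missing. The article states that one pair of inputs covers five outcomes, and its own definitions do not allow that.

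Three stronger readings are tempting, and the document does not support them.

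- *The trial lacks power for most of these outcomes.* A reader might infer this, but no outcome-specific SD, dispersion or employed share is given. The power is unsupported, not shown to be absent.
- *Objective 8 can never reach 60 per group.* The days are recorded on the electronic medical record, so a missed visit need not lose the outcome. On all 75, 60 is reached if 80% are employed (60 / 75).
- *Tablet use has an SD of 6 or more.* Betahistine is taken as needed until symptoms improve, and the protocol expects most patients may improve spontaneously after a month. The even spread over 0 to 21 is only an illustration.

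On objective 3, one may answer that with 30% relapsing the control SD is 0.46k, which is below 1.9 for up to four episodes per relapser. That is correct. But at k = 4 the implied mean difference is 4 × 0.137 = 0.55 episodes, not 1, so the 1-episode claim is not rescued.

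Finally, the 1.9 cannot be assigned to objective 5 with certainty, since a point could also be a DHI-S point.

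**Conclusion.** The point holds as a misapplied calculation. The 1-point, SD 1.9 inputs can match at most a point-scored outcome, most naturally the 0-10 severity scale, and the protocol does not say which. For the other outcomes the implied 80% power has no support in the document.

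The evidence differs by objective. For objective 8 a shortfall is likely even if SD 1.9 is granted: 66% to 43% power on 60 per group, or 76% to 52% on 75, for an assumed 70% to 40% employed. For objective 7 it is about 15% under an assumed SD of about 6 in week 1. For objective 3 the paragraph's own relapse figures give about 43%, assuming equal episodes per relapser. Objective 6 is undetermined. Objective 5 is adequately powered if its SD is 1.9. For objectives 3, 7 and 8 the calculation also does not correspond to the planned count models.

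A reader might infer that the trial is too small overall. It does not follow: the 75 per group for objectives 1 and 2 reproduces and is not affected.

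**What to change.** Reword the Sample size section as follows.

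- State which outcome the 1-point difference and SD of 1.9 were taken from, and limit the claim to it.
- For the other point-scored outcome, give the detectable difference as 0.51 times its own SD at 60 per group, with the source of that SD.
- For objectives 3, 7 and 8, give a detectable rate ratio from an assumed control rate and dispersion under the planned count model. Base objective 8 on the expected number employed. Where such inputs are not available, say that no power is claimed.

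This changes wording only and needs no extra patients. The cost is that the stated figures for several secondary outcomes will look less favourable.

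### The recurrence hazard ratio of 0.5 sits under the section's only 80% power statement, but 75 per group gives it about 45% to 53% power on the stated figures

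*Protocol article*

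**What the plan says.** The Sample size section of the protocol article opens with "Accepting an alpha risk of 0.05 and a beta risk of 0.2 in a bilateral contrast" and arrives at "approximately 75 subjects in each group (the intervention group and the control group"). The comparison behind that number is an improvement rate of "30% for the control group and 55% for the intervention group) at follow-up". The allowance for attrition follows: "We estimated a 20% rate of loss in participants (objectives 1 and 2"). The section then says that the same size also serves a 1-point difference, "assuming a standard deviation of 1.9 (objectives 3,5,6,7 and 8").

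Next comes the sentence at issue, in which relapse is counted at one year: "We estimated a recurrence hazard ratio of 0.5 in the intervention group, assuming that 30% of patients in the control group will have relapsed". It carries no objective number, sample size, event count or power of its own. The name of the sample-size software follows directly.

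Under Secondary objectives, objective 4 is the time from baseline to the first new episode. Under Statistical analysis its method is given as: "We will apply the Cox regression model to explore the effect of the intervention". The last follow-up visit is at one year.

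**The concern.** Objectives 1 and 2 are tied to the binary comparison, and objectives 3, 5, 6, 7 and 8 to the 1-point comparison. Objective 4 is the only one left, and the hazard ratio is the only assumption left to serve it. A hazard ratio and a control event rate placed in a sample-size section, below a single alpha and beta, read as part of the power case.

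Power for a Cox or log-rank comparison depends on the number of events. With 30% relapse in one arm and less in the other, 150 patients produce few events in a year.

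At stake is how the long-term result is read. The Hypothesis section claims benefit in the short, mid and long term, and the Background says that long-term evidence is scarce. If the trial is thought to have been sized for a hazard ratio of 0.5, a non-significant Cox result could be taken as evidence against a lasting benefit. At the power actually available it would be weak evidence of that.

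**Working it through.** **Inputs, all from the Sample size section.** Two-sided alpha 0.05 (z = 1.960); power 80% (z = 0.842); about 75 per group; 20% loss; 30% vs 55% improved; difference 1 with SD 1.9; hazard ratio 0.5; 30% of controls relapsed at one year. Proportional hazards is my assumption, in line with the planned Cox model.

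**Step 1. Reproduce the plan's own figure.**
- 30% vs 55%, arcsine formula: n = 2(1.960 + 0.842)² / h², with h = 2·asin(√0.55) − 2·asin(√0.30) = 0.512. This gives 59.96 per group, and 59.96 / 0.8 = 74.9.
- The pooled normal formula gives 61, or 77 after loss.
- So 75 reproduces and already includes the 20% loss. About 75 × 0.8 = 60 per group are evaluable.
- 1-point difference, SD 1.9: n = 2(1.960 + 0.842)² × 1.9² = 56.7, so 57 per group, or 72 after loss. This target is covered too.

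**Step 2. Events expected for the hazard ratio.**
- Intervention relapse at one year = 1 − 0.70^0.5 = 16.3%.
- 60 per group: 60 × (0.300 + 0.163) = 27.8 events.
- 75 per group, no loss: 75 × (0.300 + 0.163) = 34.8 events.

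**Step 3. Events needed for 80% power (Schoenfeld).**
- d = 4(1.960 + 0.842)² / (ln 0.5)² = 65.3.
- Patients per group = 65.3 / (0.300 + 0.163) = 141 evaluable, or 141 / 0.8 = 176 with 20% loss. Freedman's formula asks for more: 71 events, about 153 evaluable per group.

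**Step 4. Power at the planned size.** Power = Φ(√d / 2 × 0.693 − 1.960).

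| Basis | Events | Schoenfeld | Freedman | Simulated log-rank |
|---|---|---|---|---|
| 60 per group | 27.8 | 44.7% | 42.0% | 43.6% |
| 75 per group, 20% lost evenly over the year | 31.3 | 49.2% | – | – |
| 75 per group, no loss | 34.8 | 53.3% | 50.2% | 51.9% |

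A one-sided 5% test with no loss, which the plan does not propose, reaches 65.5%. None of the variants tried reaches 80%.

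**Step 5. Hazard ratio with 80% power.** A stronger effect yields fewer events, so the event count must be recomputed for each hazard ratio.
- 60 per group, hazard ratio 0.32: 60 × (0.30 + 1 − 0.7^0.32) = 24.5 events, power 80%. At 0.35, power is about 75%.
- 75 per group, hazard ratio 0.37: 75 × (0.30 + 1 − 0.7^0.37) = 31.8 events, power 80%.

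**Step 6. Could the input be inverted?** Suppose 30% were the share of controls still free of relapse, so that 70% had relapsed. Intervention relapse would be 1 − 0.30^0.5 = 45.2%. The need would be 65.3 / (0.700 + 0.452) = 57 evaluable per group, or 71 with 20% loss. That is close to 75.

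**The case against.** The strongest reply is that the protocol never claims 80% power for the hazard ratio. The sentence saying that the sample size also serves other comparisons lists objectives 3, 5, 6, 7 and 8 and leaves out 4. The hazard-ratio sentence has no power attached. This stands as a limit on wording: the claim is implied by placement. It does not remove the point, because the sentence has no evident purpose other than to support the sample size, and nothing marks objective 4 as outside the power statement.

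Second, 45% is the least favourable of the loss assumptions. The 20% loss is tagged to objectives 1 and 2, patients in a Cox model contribute until they are censored, and the follow-up section says that new episodes are also sought in the electronic medical record. This stands, so the range of 45% to 53% is the fair statement. A reader might infer that the trial would miss a hazard ratio of 0.5 more often than it would find it. That holds at 60 per group but not at 75 with full follow-up, so it should not be asserted.

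Third, objective 4 is one of eight secondary objectives, is not part of the primary objective's definition of improvement, and is analysed in order to explore. This bears on severity and is accepted.

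Fourth, the relapse input itself may be wrong. Step 6 makes an inversion plausible, and a reader might infer that it explains the discrepancy. The document gives no evidence beyond the numerical fit, so it is a reason to check and no more.

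**Conclusion.** The point holds as an implied power claim that the section's own figures do not support. Power for a hazard ratio of 0.5 is about 45% (60 evaluable per group, 28 events) to 53% (75 per group, no loss, 35 events), against the 80% that a reader would assume. About 65 events, or 141 evaluable per group, would be needed.

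This rests on 30% control relapse at one year as written, proportional hazards, equal allocation and a two-sided 5% test.

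Severity is moderate. A reader might infer that the trial as a whole is undersized. The document does not support that: the 75 per group reproduces for objectives 1 and 2 and also covers the 1-point target.

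**What to change.** Leave the sample size unchanged and proceed in two steps.

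1. Check the 30% relapse figure against the saved inputs of the sample-size calculation. If it was entered or reported the wrong way round, correct the sentence and give the events and power that follow.
2. If 30% is right, replace the hazard-ratio sentence with:

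> Objective 4 did not determine the sample size. With 75 per group and 28 to 35 first recurrences expected, power for a hazard ratio of 0.5 is about 45% to 53%; 80% power exists only for a hazard ratio of about 0.32 (60 evaluable per group) to 0.37 (no loss) or lower. The hazard ratio will be reported with its 95% confidence interval, and a non-significant result is not evidence of no effect.

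The cost is one check of the saved inputs and a few lines of text. Enrolment, conduct and the analyses of the other objectives do not change. The price is that one design figure becomes less favourable than the present text suggests.
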